### Design

We conducted a pragmatic randomised parallel group single-blind multi-centre trial among psoriasis patients eligible for narrowband UVB (TL-01) phototherapy. Patients were randomly allocated to two groups, thus obtaining two treatment groups of equivalent prognosis. One group was given home UVB phototherapy and the other UVB phototherapy in the outpatient department of the participating hospitals.

The design was chosen to be 'pragmatic' in order to compare the two treatments under the conditions in which they would be applied in daily practice [15]. Accordingly, in our pragmatic trial we randomised the patients into two treatment groups, but we did not impose a prespecified treatment regimen on the participants. Instead, we urged dermatologists to carry out the assigned UVB treatments as they would normally, and thus to act in accordance with their own views. Consequently, all of the implicit differences in the two treatments were compared, including factors such as frequency of irradiations, dosage, compliance, concomitant medication, support and equipment. We did not control for these and other possible differences relating to the treatment, because they cannot be controlled for in a real life situation.

The locations of the two treatments (at home versus in the outpatient department) of course made blinding of the participants impossible. Because of the pragmatic design of the study it was not desirable to blind the dermatologist. However, we arranged for the extent and severity of the psoriasis to be assessed by an independant research nurse blinded to treatment form.

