### Sample size

The sample size could not be calculated on the basis of presumed differences in effectiveness as there is no clear data available on the possible differences in treatment effects. However, based on the data available from a 1993 pilot study [16] and recent experience with home UVB phototherapy, we in fact expected the effectiveness of both therapies to be similar. The sample size was therefore calculated in accordance with a negative trial approach [17]. We considered a 50% or greater improvement in the psoriasis severity from baseline to be a relevant clinical response. A systematic review by Spuls et al. indicates that approximately 85% of the patients treated with UVB show at least a 50% improvement in their psoriasis [18]. Thus, with N = 90 per per treatment group and at α = 0.05 and β = 0.20 (power 80%), we would be able to show a difference in effectiveness of 15% or more; i.e., a reduction in effectiveness from 85% to 70% or less should be distinguishable. To allow for missing data and losses to follow-up (i.e. withdrawals, incomplete case register forms) we aimed at 100 patients per group, 200 in total. To obtain accurate estimates of the cumulative costs of UVB treatment a consecutive sample of 100 patients (50 per group) was considered to be sufficient, because little variation was expected in treatment duration, number of UVB irradiations, and use of concomitant medication.

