#### In general

In all cases the initial treatment plan was narrowband UVB phototherapy according to randomisation. No prespecified treatment regimen was imposed on the participants and adjuvant use of topical therapy was allowed to continue throughout the trial.

No other additional treatments or changes to the original treatment plan were intended. However, in order to compare the two UVB treatments under practical conditions and to reflect clinical reality, alterations to the initial treatment plan were allowed if the dermatologist decided they were necessary. As such, all treatment changes originating after inclusion and randomisation were permitted. For instance, starting any type of medication after inclusion, even systemic medication, was not considered a reason for exclusion if the dermatologist considered this treatment change necessary. Also, temporarily starting outpatient phototherapy while waiting for placement of a home phototherapy unit was allowed.

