**Figure 1 F1:**
[figure not shown]
**Timetable**. Schematic representation of successive time points for data collection, reported for all outcome measures and questionnaires. * 23 irradiations: outcome measurement was planned at approximately 23 irradiations, with a minimum of 20 and a maximum of 26 irradiations. ** End of therapy: measurement was planned at the end of the treatment. When more than 46 irradiations were needed, measurement was planned at 46 irradiations. *** Follow-up: Starting at the end of the therapy (or at the 46^th ^irradiation, see **), follow-up measurements were planned every 2 months, for up to 1 year after the last irradiation.

Immediately after this first visit, patients were randomised using the baseline data (information on the recruiting hospital and any previous experience of the patient with UV therapy were used to determine the randomisation strata). Both patient and attending dermatologist were informed about the type of treatment assigned, and the treatment was started accordingly. When (sometimes after a waiting period) the therapy was started, the patients did a SAPASI-assessment and began using the study diary. At approximately 23 (20–26) UVB treatments ànd at the end of the therapy (or 46 treatments) the patients received a series of questionnaires at home. Visits to the previously mentioned research nurse were scheduled for the same time points. Throughout the whole trial, the independent research nurse was not informed about the randomisation results and therefore remained blinded.

For all UVB therapies lasting longer than 46 treatments, a cutoff point of maximally 46 treatments was used to establish effectiveness. The choice of 46 as the maximum number of treatments was derived from unpublished data from the home care organisations about the treatment duration of their patients.

At the end of the therapy (or 46 treatments), 105 patients were followed for 12 more months to monitor long term effectiveness and cost. The patients received a short questionnaire at home every 2 months and returned this questionnaire by mail. At the end of the follow-up, information on medication use during the trial period was retrieved retrospectively for each patient from his/her pharmacist.

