## Results

Recruitment of patients was stopped after 2 years and 2 1/2 months. Initially 252 possible participants were recruited by the participating hospitals. Of these 252 patients, 56 were excluded from starting the trial for a variety of reasons. Thirty-three (33) patients had a clear preference for either home or hospital-based therapy and refused to submit to being randomised. Another 11 patients did not want to participate in a study, 6 patients did not fulfill the inclusion criteria or met one of the exclusion criteria, 2 had already started UVB therapy, 2 persons decided not to be treated with UVB, and 2 patients were excluded for other practical reasons.

Thus, in total 196 patients (252–56) were included in the study. A consecutive sample of 105 patients was followed for 12 months after the end of the treatment in order to gain sufficient data about the costs incurred after the treatment. Randomisation according to the minimisation method [19] was successful. The two factors accounted for, their levels and the number of assigned therapies are shown in table 3.

**Table 3 T3:** Results of the randomisation procedure.

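### The cost subset of about 100 patients is justified by low variation in treatment-phase items but used elsewhere for post-treatment costs, and the justification supports neither use

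*Protocol article*

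**What the plan says.** The protocol article gives the cost subset two different purposes.

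- **Sample size.** The stated aim is: "To obtain accurate estimates of the cumulative costs of UVB treatment". For this, "a consecutive sample of 100 patients (50 per group) was considered to be sufficient", and the only reason offered is "because little variation was expected in treatment duration, number of UVB irradiations, and use of concomitant medication".
- **Measurement planning.** After the end of therapy (or 46 treatments), "105 patients were followed for 12 more months to monitor long term effectiveness and cost".
- **Results.** A consecutive 105 patients were followed for 12 months "in order to gain sufficient data about the costs incurred after the treatment".

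The Costs paragraph under Statistical analysis compares costs between the two treatments and does not say which patients enter. The general Statistical analysis paragraph applies intention to treat to all included patients.

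On the conduct of treatment, the Design section states "we did not impose a prespecified treatment regimen on the participants", and the In general paragraph under UVB therapy and equipment states that "all treatment changes originating after inclusion and randomisation were permitted", systemic drugs included.

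**The concern.** A sample size for a cost comparison depends on the spread of costs and on the precision wanted. The article gives neither. It offers only an expectation that three treatment-phase quantities vary little: duration, number of irradiations and concomitant medication. That expectation is hard to square with a pragmatic trial in 14 hospitals that imposes no regimen. It also says little about costs that arise once irradiation has ended, which is the use that Measurement planning and Results describe.

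The choice of patients matters because of the rule in the Cost-effectiveness paragraph under Outcome assessment. If the difference in effectiveness is below 15%, the economic evaluation shrinks to a cost minimisation analysis. The cost difference and its confidence interval are then the whole economic answer, and the article does not say clearly whose costs they rest on.

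**Working it through.** **1. Can the 100 be reproduced?** No. The article gives no standard deviation, coefficient of variation, cost difference, precision target or power for costs, so the figure can be neither derived nor refuted.

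**2. Does the article support low variation?** Its own provisions for the three named items are:

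| Item | Provision | Where |
|---|---|---|
| Duration | Outpatient: each hospital's own schedule, 2–3 irradiations a week. Home: at least 3–4 a week | In the outpatient department; At home |
| Number of irradiations | Interim visit at 20–26; courses longer than 46 provided for | Measurement planning |
| Concomitant medication | Topical treatment may continue; any drug may be added | In general |

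The frequency contrast between home and hospital is a difference between arms and does not add to within-arm variance, so I look inside the outpatient arm only. A course of 23 irradiations at 3 a week lasts 23/3 = 7.7 weeks, and one of 46 at 2 a week lasts 46/2 = 23 weeks. The rules thus allow a threefold range within one arm. Results adds that seven patients never started and five switched, and all of them stay in an intention-to-treat cost comparison.

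This shows that wide variation is permitted and provided for. It does not show how large the variation was.

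**3. What would restricting treatment-phase costs to the subset cost in precision?**

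Inputs: 50 per group (Sample size); 105 in total (Results), taken as 52.5 per group because the split is not given; 98 per group for the full trial (Table 3: 50 + 48 in each arm). The standard deviation is assumed equal in both arms and the same in subset and full sample.

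95% CI half-width for a difference in means = 1.96 × SD × √(2/n):

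- n = 50: 1.96 × √(2/50) = 0.392 SD
- n = 52.5: 1.96 × √(2/52.5) = 0.383 SD
- n = 98: 1.96 × √(2/98) = 0.280 SD

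Ratios to the full sample: √(98/50) = 1.40 and √(98/52.5) = 1.37. Conversely, moving to all 196 narrows the interval by 1 − √(100/196) = 29% or 1 − √(105/196) = 27%.

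Power for a true difference of 0.4 SD (an illustrative value, two-sided 5%) is 52% with 50 per group, 54% with 52.5 and 80% with 98.

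**4. What might that mean in money?** The article gives no coefficient of variation (CV), so the values below are assumptions. The half-width is a percentage of mean cost:

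| Assumed CV | 50 per group | 98 per group |
|---|---|---|
| 0.2 | 7.8% | 5.6% |
| 0.5 | 19.6% | 14.0% |
| 1.0 | 39.2% | 28.0% |
| 1.5 | 58.8% | 42.0% |

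At a CV of 0.2 the subset might well be enough. At 1.0 it would be a weak basis for cost minimisation. The low-variation sentence is all the article offers to choose between these cases.

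**5. Are treatment-phase data available beyond the subset?** Dosimetry describes diaries of treatment times for both groups and copied charts for outpatient participants. Costs (under Outcome assessment) describes diary and questionnaire data on expenses. Measurement planning describes questionnaires at about 23 irradiations and at the end of therapy. None of these is limited to the subset.

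**The case against.** The strongest reply is that the article never says treatment-phase costs will be analysed in the subset alone. A reader might infer from the Sample size sentence that 91 randomised patients are to be discarded. The documents do not establish that: the other sections treat the subset as a follow-up sample, treatment-period data are described for participants generally, and the analysis text covers all included patients. This stands. The loss of precision is therefore conditional on following the Sample size wording.

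A reader might also say that the trial's rules contradict the low-variation premise. That goes too far. Permissions are not observed spread, and no proportion of courses beyond 46 is given. Systemic antipsoriatic drugs in use at inclusion were an exclusion, no treatment changes were intended at the outset, and 184 of 196 patients were treated as randomised. The premise is unsupported, not refuted.

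Nor does it follow that a consecutive subset loses the balance given by minimisation. Minimisation on hospital and previous UV therapy works patient by patient, so a consecutive run should stay close to balanced on those factors, and no imbalance in the 105 is shown. Eight hospitals joined late, which may affect how well the subset represents the trial, but the article does not say which stretch of recruitment it covers. Standardising 105 patients to up to 28 hospital-by-previous-UV cells (14 × 2) would be impractical.

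What survives the reply is the conflict of purpose and a rationale that fits neither purpose.

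**Conclusion.** The point holds in a limited form. The sections disagree on what the subset is for, and its stated justification fails either way: it lacks any supporting figure for treatment costs and is largely irrelevant to post-treatment costs.

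If the Sample size wording were followed, the treatment-phase interval would be 37% to 40% wider than it need be. That figure assumes equal variances, an even split of the 105, and usable treatment-period records for all 196. It does not carry over to the 12-month total used for cost-effectiveness, because post-treatment costs can come only from the 105. The gain for that total cannot be computed without the separate variances.

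Medication costs are uncertain. The statement that pharmacist data were retrieved for each patient follows directly on the account of the 105 and is timed at the end of follow-up, so it may cover only those followed.

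The main sample size for effectiveness is not affected.

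**What to change.** 1. Reconcile Sample size, Measurement planning, Results and the Costs paragraph of Statistical analysis, and state which patients enter each cost component.
2. Estimate treatment-phase costs in all 196 randomised patients from the diaries, charts and questionnaires.
3. Use the 105 only for post-treatment costs and long-term follow-up, and report their number per arm.
4. State whether pharmacist data cover all patients or only those followed.
5. Drop the low-variation rationale, or replace it with the precision expected for the cost difference and the standard deviation behind it.

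The cost is the work of costing existing records for about 91 more patients (196 − 105) and a few sentences of text. Diary-, chart- and questionnaire-based costs need no new data collection. If treatment-phase costs were always meant to cover all 196, only the wording changes.

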### Recruitment

#### Hospitals

We planned to include two hundred patients in approximately 2 years' time, starting October 2002. To achieve this, several hospitals were invited to join the study. Initially five university hospitals and one closely related non-university hospital agreed to participate. Later on, when inclusion of patients fell short of expectations, another eight hospitals were recruited from the same districts or nearby. In total 14 hospitals took part in the trial; 5 university hospitals and 9 non-university hospitals.

#### Patients

When the dermatologists of the collaborating hospitals prescribed UVB phototherapy to a patient, they checked eligibility for the trial using the above-mentioned list of inclusion and exclusion criteria (table 1). If all criteria were met, patients were informed about the possibility of participating. If the patient was interested, he/she received written information to take home. The same day the central coordination centre (UMC Utrecht) was provided with the name and phone number of the patient.

After 1–2 days the investigators at the central coordination centre contacted the patient by telephone and provided additional information. During this conversation the principle of randomisation (no choice of treatment) was explained at length, and eligibility criteria were checked again. If after reading and hearing the information and being allowed to ask additional questions patients were still interested in participating, a visit for inclusion and informed consent was scheduled as soon as possible. Patients not included in the trial were allowed to start their UVB therapy of choice without any further delay.

### Randomisation procedure

Every patient eligible for UVB phototherapy who was willing to participate in the study was registered at the central coordination centre. After providing informed consent and registration of baseline data a randomisation number corresponding with either home or outpatient phototherapy was drawn from a computer-generated list. Randomisation took place using stratified randomisation, in particular the minimisation method described by Pocock [19]. This method assigned the two treatments taking into account the recruiting hospital and possible previous experiences with UV phototherapy. After randomisation, both patient and dermatologist were informed of the assigned treatment, and this treatment was started according to standard procedures.

### UVB therapy and equipment

#### In the outpatient department

Patients randomised to the group treated in the outpatient department received the UVB treatment in their own hospital. The type of irradiation was restricted to narrowband UVB (TL-01 tubes) [20]. All hospitals used their own treatment schedules and their own (full circle) cabins. Some types of cabins had UV indicators measuring irradiation intensity (mW/cm^2^); others did not and measured only treatment time. For cabins with intensity indicators, treatment schedules were formulated in dosage (J/cm^2^). For cabins without intensity indicators, treatments were prescribed in units of time (seconds). Neither equipment nor schedules were modified for the trial. The frequency of irradiation was 2–3 times a week, depending on the hospital.

#### At home

When patients were assigned to have home UVB phototherapy, the investigator placed an order with one of the two home care organisations that provide the vast majority of home UV phototherapy in the Netherlands [14]. Orders were divided equally between the two organisations, taking into account equal distributions per hospital and the preferences of the patient's insurance company (reimbursement). The UVB treatment was administered in the patient's home, using equipment provided by one of the home care organisations. The home phototherapy units used were Waldmann UV-100 units with TL-01 lamps. This device comprises a semi-circular arrangement of lamps. These units do not have an irradiation intensity indicator; therefore treatments were prescribed in units of time. The patients were instructed and supervised in the use of the equipment by the nursing staff of the home care institutions. The treatment schedules were the schedules normally used by those institutions. Neither equipment nor schedules were modified for the trial. The frequency of irradiation was at least 3–4 times a week (i.e. once every 2 days, sometimes starting daily).

#### In general

In all cases the initial treatment plan was narrowband UVB phototherapy according to randomisation. No prespecified treatment regimen was imposed on the participants and adjuvant use of topical therapy was allowed to continue throughout the trial.

No other additional treatments or changes to the original treatment plan were intended. However, in order to compare the two UVB treatments under practical conditions and to reflect clinical reality, alterations to the initial treatment plan were allowed if the dermatologist decided they were necessary. As such, all treatment changes originating after inclusion and randomisation were permitted. For instance, starting any type of medication after inclusion, even systemic medication, was not considered a reason for exclusion if the dermatologist considered this treatment change necessary. Also, temporarily starting outpatient phototherapy while waiting for placement of a home phototherapy unit was allowed.

### Outcome assessment

To answer the separate research questions, several outcome assessments had to be performed during the trial. The majority of the outcomes were measured using questionnaires or were assessed by an independent, blinded research nurse.

#### Effectiveness

We assessed the effectiveness of both treatments using the Psoriasis Area and Severity Index (PASI) [21] and the Self-Administered PASI (SAPASI) [22]. Both indices evaluate the severity of the psoriatic lesions ànd the area of psoriatic involvement. Their scores vary from 0.0 (no lesions at all) to 72.0 (complete erythroderma of the severest possible degree) [21]. An independent and blinded research nurse administered the PASI during several patient visits to the outpatient clinic. The SAPASI was easier to collect using a questionnaire and was used as an equivalent of the PASI as well as an indicator of the patient's own impression of the extent of the psoriasis lesions [22,23] Both the PASI and the SAPASI were assessed for the whole body, including the lower legs and the scalp. We also determined skin type according to Fitzpatrick's classification of skin phototypes [24,25] and collected data on concomitant use of medication, side effects, demographics and past medical history.

#### Dosimetry

We routinely measured the light intensity (*J/cm^2^*) of all UVB equipment from the hospitals with a small portable Waldmann UV meter, type 585 100 (Villingen, Schwenningen, Germany), referred to as meter A. If the cabin had an irradiation intensity indicator, we compared its reading with our own measurements. To collect information about calculated treatment doses (*mW/cm^2^*), we made copies of the treatment charts of the participants treated in the outpatient departments.

The home care organisations measured the light intensity of every unit before the first irradiation and after the last irradiation, using their own small Waldmann UV meters, all type 585 100, referred to as meters B. At the end of the trial we collected these measurements and compared their meters (B) with our own Waldmann UV-meter (A), calibrated with the High Accuracy UV-Visible Spectroradiometer, type OL 752 (Orlando, Florida, U.S.A.).

Both groups of participants kept a record of their treatment times in their diary. For all patients we calculated standardised cumulative doses using the intensity measurements together with the individual treatment charts and/or diaries. The way cumulative doses were standardised in this trial is described in table 2.

**Table 2 T2:** Calculation of standardised cumulative doses for the three different situations in the trial.

**Situation**	**Treatment location**	**UVB equipment**	**Treatment schedule**	**Cumulative Dose (CD)**	**Standardisation factor F**
1	In the hospital	With intensity indicator	in J/cm^2^	*CD *= *CD*_*h *_× *F*	F=IAIh×IsrIcA MathType@MTEF@5@5@+=feaafiart1ev1aaatCvAUfKttLearuWrP9MDH5MBPbIqV92AaeXatLxBI9gBaebbnrfifHhDYfgasaacH8akY=wiFfYdH8Gipec8Eeeu0xXdbba9frFj0=OqFfea0dXdd9vqai=hGuQ8kuc9pgc9s8qqaq=dirpe0xb9q8qiLsFr0=vr0=vr0dc8meaabaqaciaacaGaaeqabaqabeGadaaakeaacqWGgbGrcqGH9aqpdaWcaaqaaiabdMeajnaaBaaaleaacqWGbbqqaeqaaaGcbaGaemysaK0aaSbaaSqaaiabdIgaObqabaaaaOGaey41aq7aaSaaaeaacqWGjbqsdaWgaaWcbaGaem4CamNaemOCaihabeaaaOqaaiabdMeajnaaBaaaleaacqWGJbWycqWGbbqqaeqaaaaaaaa@3DD2@
2	In the hospital	Without intensity indicator	in time (seconds)	*CD *= *CTT *× *I*_*A *_× *F*	F=IcAIcA×IsrIcA MathType@MTEF@5@5@+=feaafiart1ev1aaatCvAUfKttLearuWrP9MDH5MBPbIqV92AaeXatLxBI9gBaebbnrfifHhDYfgasaacH8akY=wiFfYdH8Gipec8Eeeu0xXdbba9frFj0=OqFfea0dXdd9vqai=hGuQ8kuc9pgc9s8qqaq=dirpe0xb9q8qiLsFr0=vr0=vr0dc8meaabaqaciaacaGaaeqabaqabeGadaaakeaacqWGgbGrcqGH9aqpdaWcaaqaaiabdMeajnaaBaaaleaacqWGJbWycqWGbbqqaeqaaaGcbaGaemysaK0aaSbaaSqaaiabdogaJjabdgeabbqabaaaaOGaey41aq7aaSaaaeaacqWGjbqsdaWgaaWcbaGaem4CamNaemOCaihabeaaaOqaaiabdMeajnaaBaaaleaacqWGJbWycqWGbbqqaeqaaaaaaaa@4022@
3	At home	Without intensity indicator	in time (seconds)	CD=CTT×IB1+IB22×F MathType@MTEF@5@5@+=feaafiart1ev1aaatCvAUfKttLearuWrP9MDH5MBPbIqV92AaeXatLxBI9gBaebbnrfifHhDYfgasaacH8akY=wiFfYdH8Gipec8Eeeu0xXdbba9frFj0=OqFfea0dXdd9vqai=hGuQ8kuc9pgc9s8qqaq=dirpe0xb9q8qiLsFr0=vr0=vr0dc8meaabaqaciaacaGaaeqabaqabeGadaaakeaacqWGdbWqcqWGebarcqGH9aqpcqWGdbWqcqWGubavcqWGubavcqGHxdaTdaWcaaqaaiabdMeajnaaBaaaleaacqWGcbGqcqaIXaqmaeqaaOGaey4kaSIaemysaK0aaSbaaSqaaiabdkeacjabikdaYaqabaaakeaacqaIYaGmaaGaey41aqRaemOrayeaaa@4108@	F=IcAIcB×IsrIcA MathType@MTEF@5@5@+=feaafiart1ev1aaatCvAUfKttLearuWrP9MDH5MBPbIqV92AaeXatLxBI9gBaebbnrfifHhDYfgasaacH8akY=wiFfYdH8Gipec8Eeeu0xXdbba9frFj0=OqFfea0dXdd9vqai=hGuQ8kuc9pgc9s8qqaq=dirpe0xb9q8qiLsFr0=vr0=vr0dc8meaabaqaciaacaGaaeqabaqabeGadaaakeaacqWGgbGrcqGH9aqpdaWcaaqaaiabdMeajnaaBaaaleaacqWGJbWycqWGbbqqaeqaaaGcbaGaemysaK0aaSbaaSqaaiabdogaJjabdkeacbqabaaaaOGaey41aq7aaSaaaeaacqWGjbqsdaWgaaWcbaGaem4CamNaemOCaihabeaaaOqaaiabdMeajnaaBaaaleaacqWGJbWycqWGbbqqaeqaaaaaaaa@4024@

*CD *= Cumulative Dose (*J/cm^2^*) standardised for the study.

*CD*_*h *_= Cumulative Dose (*J/cm^2^*) as calculated by the hospital (retrieved from treatment chart).

*CTT *= Cumulative Treatment Time (*s*) as retreived from the diary and/or treatment chart.

*F *= correction factor for standardisation.

Measurements on location:

*I*_*A *_= Intensity (*mW/cm^2^*) as measured by the investigators for each hospital UVB unit with portable intensity meter A.

*I*_*h *_= Intensity (*mW/cm^2^*) as simultaneously measured by the hospitals' UVB unit irradiation intensity indicator.

*I*_*B*1 _= Intensity (*mW/cm^2^*) measured by the home care organisations before start of first treatment, using their meters (B).

*I*_*B*2 _= Intensity (*mW/cm^2^*) measured by the home care organisations after finishing last treatment, using their meters (B).

Measurements during calibration:

*I*_*cA *_= Intensity (*mW/cm^2^*) as measured during calibration by the investigators' portable intensity meter A.

*I*_*cB *_= Intensity (*mW/cm^2^*) as measured during calibration by the intensity meters (B) of the home care organisations.

*I*_*sr *_= Intensity (*mW/cm^2^*) as measured during calibration with the High Accuracy Spectroradiometer type OL 752

